### Intervention and blinding

Active arm subjects will switch their warfarin use to morning. The control arm will continue with their current pattern of evening use. There are no run-in or washout periods in this study. Participants randomized to morning warfarin ingestion will be asked to make the change 5 days prior to their next scheduled INR test (so that any deviation in the INR can be detected early). Although patients and their physicians will be aware of treatment assignment, our study evaluators will be blinded to allocation.

### On-study participant interaction

Participants have the option to interact with study staff either online (via online consent and online follow-up surveys using REDCap) or in person (via mailing in consent and having follow-up interviews over the phone where study staff record their responses in REDCap). Following the randomization telephone interview, such online or in-person follow-up interviews then occur at 1 week, 1 month, and 7 months (relative to the expected date of first morning ingestion of warfarin in those allocated to morning use, or relative to the date of randomization in those allocated to control). During these interviews participants self-report their adherence to the allocated timing of warfarin ingestion, as well as any illnesses and potentially warfarin-related adverse events (bleeding and thromboembolic events). Patients are encouraged to adhere to the allocated intervention during telephone follow-up, and suggestions to facilitate adherence at the time of allocation include: (1) helping to set a routine by placing their warfarin near objects that they interact with at the relevant time of day (e.g., other medications, toothbrush, false teeth, coffee pot/kettle/toaster), (2) using a dosette box with time of day divisions, (3) setting an alarm, (4) asking their spouse to remind them, and (5) offering to have study staff remind them the day before any switch to morning warfarin is supposed to occur. Decisions on discontinuing warfarin or returning to evening dosing in response to perceived harm, or upon patient request, will be made entirely by the treating physician at their discretion. The same is true for any decisions related to concomitant care. Participants are free to withdraw from the study at any time without penalty and can decide to have their data excluded from, or continue to be included in, the analysis.

### Outcomes

Seven months after randomization of each patient, we will ask their family physician to provide us all INR results for that period in order to determine the following outcomes during the last 6 months of therapy.

#### Primary outcome

The primary outcome is percentage change in time spent *outside* the family physician’s target INR range for that patient. This primary outcome has been chosen because we believe this is a measure more likely to be shared by patients across a wide range of TTR. It is also the time spent outside of range that contributes more directly to risk of thrombosis and hemorrhage; hence, the change in this measure is more clinically meaningful than the change in TTR itself.

#### Secondary outcomes

The secondary outcomes are:Change in TTRPercentage of patients with TTR >75 %Percentage of patients with TTR <60 %For those patients with at least one INR value above the therapeutic range, the maximum INR value observedFor those patients with at least one INR value below the therapeutic range, the minimum INR value observedPercentage of time spent above the therapeutic rangePercentage of time spent below the therapeutic rangeMajor warfarin-related cardiovascular events (including all-cause mortality, hospitalization for stroke, hospitalization for GI bleeding, and deep venous thrombosis/pulmonary embolism)

The percentage of patients with TTR >75 % provides the percentage of patients considered to have excellent control, while the percentage of patients <60 % provides the percentage of patients for whom other anticoagulation strategies may be indicated [6, 7]. Maximum and minimum INR values provide a sense of how far out of range patients go, while major warfarin-related cardiovascular events aggregate outcomes that might stem from both inadequate and excessive anticoagulation.

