### Hypotheses

Our hypotheses are as follows:Morning, as compared to evening, administration of warfarin will produce a more consistent anticoagulant effect and improve the proportion of time a patient spends in the target therapeutic INR range (TTR = time in therapeutic range).A less variable day-to-day dietary vitamin K consumption at dinner, whether consistently high or consistently low, will reduce variability in the anticoagulant effect of warfarin and improve the proportion of time a patient spends in the target therapeutic INR range.

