#### RCT

All analyses will be by intention to treat. The primary analysis of percentage change in time outside of therapeutic range will be by Student’s *t* test if the data appear to be normally distributed or by Mann-Whitney U test if they are not. As percentage change in time outside of therapeutic range can only be calculated for patients for whom the time outside normal range is not zero, this analysis will exclude anyone who was in range 100 % of the time at baseline. The secondary analyses will be by Student’s *t* test or Mann-Whitney U test (for percentage change in TTR, maximum and minimum INR values, and percentage of time spent above and below target range) and by Student’s *t* test or Fisher’s exact test (for both percentages of patients with TTR >75 % and <60 %, and major warfarin-related cardiovascular events). A subgroup analysis of the influence on the intervention of the numbers of days per week that high vitamin K foods are ingested will be carried out looking at an ANOVA analysis of percent change in time outside of therapeutic range according to three possible categories for the number of days per week of consumption of high vitamin K-containing foods (these being less than 2, 2 to 5, and greater than 5 days per week). In the same analysis we will also examine the effect on the intervention of the patient’s global assessment of how variable their consumption of high vitamin K containing foods is. To do this, we will convert the 4-point scale of possible responses into a dichotomous variable that combines the two options indicating the most variable diet and the two options indicating the least variable diet.

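### Maximum and minimum INR are compared between arms only in patients who left range after randomisation, so these two secondary comparisons lose the protection of randomisation and can be attenuated or reversed

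*Protocol article*

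**What the plan says.** All of this is in the protocol article.

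- **Secondary outcomes** defines one outcome for "those patients with at least one INR value above the therapeutic range, the maximum INR value" and its mirror image for "those patients with at least one INR value below the therapeutic range, the minimum INR value". The stated purpose is: "Maximum and minimum INR values provide a sense of how far out of range patients go".
- **Outcomes** says that the INR results are obtained "in order to determine the following outcomes during the last 6 months of therapy", so the qualifying out-of-range value arises after randomisation.
- **RCT** (under Statistical analysis) assigns Student's t test or the Mann-Whitney U test to "percentage change in TTR, maximum and minimum INR values, and percentage of time spent above and below target range". It gives no value to patients who never left range and does not label the restricted comparison as descriptive.
- **Hypotheses** states that morning dosing "will produce a more consistent anticoagulant effect and improve the proportion of time a patient spends in the target therapeutic INR range".
- Percentage of time above range and percentage of time below range are also secondary outcomes, without any restriction on patients.

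**The concern.** Having at least one value above (or below) range is itself a result of treatment. If morning dosing works as hypothesised, it changes who qualifies. Patients whose INR would have strayed only slightly stay in range and drop out of the morning subset, while the more erratic patients remain. The subset mean then mixes two things: how far patients stray, and which patients are left to be counted.

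At stake is the trial's reading on depth of excursion. A real benefit may look smaller than it is, or look like harm, and a real harm may look like benefit. The restriction is also unnecessary, because every patient with follow-up INRs has a maximum and a minimum.

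**Working it through.** **The plan's own figure.** The only computed figure is the sample size for the primary outcome: n per group = 2 × (1.960 + 1.282)² × (40/20)² ≈ 84.1, rounded up to 85, which reproduces the article's 85. Enrolment of 200 corresponds to 170/0.85. Nothing below changes these figures.

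**Inputs.** From the article: a range one INR unit wide (midpoint ± 0.5) and 85 per arm. Assumed, because the article gives no figures: midpoint 2.5; nine independent, normally distributed INRs per patient; 70 % stable patients with within-patient SD σ = 0.45; 30 % unstable with σ = 0.80. The minimum behaves the same way by symmetry.

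**Formulas**, for a patient with SD σ:
- Chance of at least one value above 3.0: P = 1 − Φ(0.5/σ)⁹.
- Mean excess of the maximum over 3.0, counted as 0 if never above: E = ∫ [1 − Φ(x/σ)⁹] dx, from x = 0.5 upward.
- Restricted mean maximum (as the article defines it) = 3 + (weighted E)/(weighted P).
- All-patient mean maximum = 2.5 + 1.485 × (weighted σ), where 1.485 is the expected maximum of nine standard normal values.

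Numerical values:

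| σ | P | E |
|---|---|---|
| 0.45 | 0.724 | 0.208 |
| 0.80 | 0.938 | 0.698 |
| 0.27 | 0.254 | 0.0285 |

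**Benefit confined to stable patients (0.45 to 0.27).**
- Evening: P = 0.7 × 0.724 + 0.3 × 0.938 = 0.788; E = 0.7 × 0.208 + 0.3 × 0.698 = 0.355; restricted mean = 3 + 0.355/0.788 = 3.45.
- Morning: P = 0.7 × 0.254 + 0.3 × 0.938 = 0.459; E = 0.7 × 0.0285 + 0.3 × 0.698 = 0.229; restricted mean = 3 + 0.229/0.459 = 3.50.
- All patients: 2.5 + 1.485 × 0.555 = 3.324 evening; 2.5 + 1.485 × 0.429 = 3.137 morning.

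Unstable patients make up 0.3 × 0.938/0.788 = 36 % of the evening subset but 0.3 × 0.938/0.459 = 61 % of the morning subset. That shift alone produces the apparent harm.

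**Scenarios side by side** (morning minus evening):

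| Scenario | Enter subset, evening / morning | Restricted mean maximum | All-patient mean maximum |
|---|---|---|---|
| No effect | 79 % / 79 % | 0 | 0 |
| All SDs cut by 15 % | 79 % / 69 % | −0.09 | −0.12 |
| Benefit in unstable only (0.80 to 0.68) | 79 % / 78 % | −0.06 | −0.05 |
| Benefit in stable only (0.45 to 0.27) | 79 % / 46 % | +0.05 | −0.19 |
| Harm in stable only (0.27 evening, 0.36 morning) | 46 % / 66 % | −0.07 | +0.09 |

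**At 85 per arm** (simulated trials, Mann-Whitney test). With the stable-only benefit, the restricted means favour evening in about 72 % of trials. The restricted test correctly detects the benefit in about 3 %, against about 98 % when all patients' maxima are used and about 97 % when excess over the limit with zeros is used. With the uniform 15 % cut, detection is about 30 % restricted and about 53–55 % in all patients.

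**Number of tests.** In the stable-only scenario the restricted difference is +0.06 with 6 tests per patient and +0.03 with 12. With 20 tests it is −0.03, against an all-patient difference of 3.301 − 3.536 = −0.235: no longer reversed, but heavily attenuated.

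**The case against.** The case for leaving the plan alone has four parts.

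1. *Reversal needs a particular pattern.* The benefit has to be concentrated in the more stable patients, and nothing in the background, hypotheses or aims predicts that. The aims only ask whether dietary variability modifies the effect. With a uniform benefit the direction is right, and with a benefit in unstable patients there is no attenuation. This stands: a reader might infer that the comparison will point the wrong way, and the documents do not support that. It can do so; it need not.
2. *A false significant harm is unlikely.* In the stable-only scenario above, a significant wrong-direction result occurs in only about 3 % of simulated trials. This also stands for that scenario. Under other assumed inputs, with half the patients benefiting, the rate was about 12 % for a 30 % cut in SD and 35 % for a 45 % cut. Loss of a real signal is the more consistent cost.
3. *Other outcomes cover the gap.* Time above and time below range are unrestricted and tested, so a reader could see fewer or shorter excursions beside an odd maximum. This is a partial mitigation only, because those outcomes measure duration, not depth.
4. *Intention to treat is not breached.* A reader might infer that the restriction contradicts "All analyses will be by intention to treat". The documents do not clearly support that. The statement can be read as governing analysis by allocated arm, while the restriction belongs to the declared outcome definition. The sound criticism is selection after randomisation, and it does not depend on that sentence.

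Nor can the point be put down to detail left for an unseen analysis plan: the restriction and the between-arm tests are both written in the article.

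**Conclusion.** The point holds for two secondary outcomes. As defined, the comparisons of maximum and minimum INR are between subsets formed after randomisation by an event that the intervention is expected to influence, so they have no straightforward causal reading. Under the assumed inputs the consequence ranges from none (no effect at all), through attenuation (−0.09 against −0.12), to reversal (+0.05 against −0.19), and a harm in stable patients can appear as benefit (−0.07 against +0.09). The structural flaw does not depend on those inputs. The sizes do: the SDs, the mix of patients, the number of tests and the normal model are all assumptions. The primary outcome, the sample size and the other secondary outcomes are untouched.

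**What to change.** Redefine both outcomes for all randomised patients with follow-up INRs: the largest excursion above the patient's own upper limit, and the largest below the lower limit, each set to 0 if the patient never went beyond it. Compare arms with the Mann-Whitney test already named in the plan, because the zeros rule out a normal shape. An acceptable alternative is the maximum and minimum expressed as distance from the patient's target midpoint. Either form also handles target ranges that differ between patients.

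Keep the restricted maximum and minimum as descriptive summaries without a test, shown beside the proportion of each arm that had an excursion.

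Do not adjust for the number of INR tests, even though extremes grow with testing. That number is measured after randomisation, and an out-of-range result may itself prompt more tests. Report it by arm instead.

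The cost is a sentence or two in the outcome list and the analysis section. No new data are needed, since all INR results for the period are already to be collected. The small downside is that the all-patient measure mixes frequency and depth of excursions, which the descriptive summaries help to separate.

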### Randomization and allocation

Upon receiving eligible baseline INR data, consented eligible participants are contacted by a study coordinator via telephone to obtain baseline information presumed to be predictive of TTR. This includes age ≥80 years, hospitalization in the last 6 months, temporary planned discontinuation of warfarin in the last 6 months (e.g., for elective surgery), number of daily prescription medications, <6 months of warfarin use, the self-reported average number of days per week in which high vitamin K-containing foods are consumed, and how variable the participant feels this estimated level of vitamin K consumption is (on a 4-point scale). This study coordinator (who has no clinical patient interactions) then randomizes the participant, using the REDCap^TM^ randomization module to ensure allocation concealment, to intervention or control [5]. Randomization will employ variable blocks of 2 or 4 and will be stratified by the proportion of baseline INR readings within the therapeutic range (<50 %, 50–80 %, >80 %).

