### Sample size

We wish to be able to demonstrate a 20 % reduction in time out of therapeutic range and will conservatively estimate (since there are no prior studies exploring this outcome to guide us) that the standard deviation of this measure is twice the mean effect (i.e., SD = 40 %). For a *t* test with 1:1 allocation to the control and experimental groups, power = 0.9, alpha = 0.05, minimum difference = 20 %, and SD = 40 %, the required sample size per group is 85 (i.e., 170 subjects in total). Providing for potential dropouts, we will increase our target enrollment to 200 subjects.

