### Statistical analysis

#### Calculating TTR

The therapeutic INR range for each patient will vary and be determined by the treating physician. Typically the therapeutic range is 1 unit wide (often 2–3 or 2.5–3.5), but some physicians will choose narrower or wider ranges (e.g., 3.0–3.5 or 2–3.5). We will standardize the width of all target ranges by determining the midpoint of each patient’s individual target range and use upper and lower limits that are 0.5 unit above and below this midpoint. For example, if a physician is targeting a narrower than normal 3.0–3.5 range, we will use a midpoint of 3.25 and assume a (standardized width) target therapeutic range of 2.75–3.75. The proportion of time both in and out of therapeutic range will be determined using the linear interpolation method of Rosendaal, which (conceptually) draws a line between sequential INR values no more than 8 weeks apart and assigns a projected INR value to every day in that interval [8].

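### Maximum and minimum INR are compared as raw values although target midpoints differ between patients, so across patients with different midpoints these two secondary outcomes do not consistently show how far out of range a patient went

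*Protocol article*

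**What the plan says.** - **Outcome definition.** The Protocol article, Secondary outcomes, takes the highest observed INR in patients with at least one value above range, and the lowest observed INR in patients with at least one value below it. The stated purpose is that "Maximum and minimum INR values provide a sense of how far out of range patients go".
- **Target ranges.** Under Calculating TTR, "The therapeutic INR range for each patient will vary and be determined by the treating physician". The article adds: "Typically the therapeutic range is 1 unit wide (often 2–3 or 2.5–3.5", and mentions 3.0–3.5 and 2–3.5 as narrower and wider choices.
- **Standardization.** The same section finds the midpoint of each patient's range and will "use upper and lower limits that are 0.5 unit above and below this midpoint". For a 3.0–3.5 target the plan will "assume a (standardized width) target therapeutic range of 2.75–3.75". Widths become equal; midpoints stay different.
- **Analysis.** Under RCT, Student's t test or the Mann-Whitney U test is applied to "maximum and minimum INR values, and percentage of time spent above and below target range", among others. No rescaling to the patient's range and no adjustment for it is stated.
- **Randomization.** Allocation is "stratified by the proportion of baseline INR readings within the therapeutic range". Target range is not a stratification factor.

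**The concern.** Distance out of range needs a reference limit. Time outside, inside, above and below range are all judged against the patient's own range. That range even decides who enters the maximum and minimum INR comparisons, but the score then drops it. Across patients with different midpoints, the score therefore mixes depth of excursion with the level at which the physician chose to hold the INR.

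That level is fixed before randomization and has nothing to do with the timing of the dose. At stake is the reading of two tested secondary outcomes: a difference between arms could not be read cleanly as a difference in depth of excursion, and variation in target level adds noise to both tests.

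**Working it through.** **The plan's own figure.** The only power calculation is for the primary outcome: "power = 0.9, alpha = 0.05, minimum difference = 20 %, and SD = 40" per cent. Taking alpha as two-sided (an assumption), n = 2 × (1.960 + 1.282)² × (40/20)² = 84.1, rounded up to 85 per group, as stated. This point does not touch it.

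**Limits used for TTR (midpoint ± 0.5)**

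| Physician's range | Midpoint | Limits |
|---|---|---|
| 2–3 | 2.5 | 2.0–3.0 |
| 2.5–3.5 | 3.0 | 2.5–3.5 |
| 3.0–3.5 | 3.25 | 2.75–3.75 |
| 2–3.5 | 2.75 | 2.25–3.25 |

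The two common ranges differ by 0.5 at both ends, exactly and without assumption.

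**Illustrative pairs on the two common ranges**

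| Outcome | On 2–3 | On 2.5–3.5 | Raw order | Order by distance |
|---|---|---|---|---|
| Maximum | 3.6 − 3.0 = 0.6 | 3.6 − 3.5 = 0.1 | tied | first is worse |
| Maximum | 3.6 − 3.0 = 0.6 | 3.7 − 3.5 = 0.2 | second is worse | first is worse |
| Minimum | 2.0 − 1.7 = 0.3 | 2.5 − 1.8 = 0.7 | first is worse | second is worse |

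**General rule.** Let a be the distance beyond the limit on 2–3 and b the distance on 2.5–3.5. The raw maxima are 3 + a and 3.5 + b, so the order is reversed when 0 < a − b < 0.5. The raw minima are 2 − a and 2.5 − b, so the order is reversed when 0 < b − a < 0.5. With one midpoint the offset is zero and nothing is reversed.

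**Size, closed form.** The article gives neither the mix of ranges nor the distribution of excursions, so both are assumed here. A share p is on 2.5–3.5 and the rest on 2–3; the excursion above the limit is exponential with mean m in both groups.

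- Reversed among mixed-range pairs: 0.5 × (1 − exp(−0.5/m))
- Reversed among all pairs: 2p(1 − p) times that
- Variance of the raw value relative to the distance: 1 + 0.25 p(1 − p)/m²

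| m | Mixed pairs reversed | All pairs reversed, p = 10–30 % | Variance ratio, p = 10–30 % |
|---|---|---|---|
| 0.3 | 41 % | 7–17 % | 1.25–1.58 |
| 0.5 | 32 % | 6–13 % | 1.09–1.21 |
| 1.0 | 20 % | 4–8 % | 1.02–1.05 |

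**Size, simulated.** A second set of assumptions treats the two outcomes separately: 7 INRs per patient, log-normal about the midpoint, log-SD 0.20–0.30, rounded to 0.1, restricted to patients with a value beyond the limit.

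| Assumption | Variance ratio, maximum | Variance ratio, minimum |
|---|---|---|
| Same log-SD for all, 10–30 % on 2.5–3.5 | 1.09–1.56 | 1.17–2.27 |
| Same log-SD for all, 2–5 % on 2.5–3.5 | 1.02–1.16 | 1.04–1.43 |
| Log-SD varying between patients (CV 0.3–0.5), 10–30 % on 2.5–3.5 | about 1.02–1.26 | about 1.1–1.8 |

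In the first row, mixed-range pairs with different distances are reversed in about 16–26 % (maximum) and 43–56 % (minimum). Over all pairs with different distances this is about 3–12 % and 8–26 %. In the third row, the mixed-pair figures fall to about 13–23 % and 31–47 %. The minimum suffers more because distances below range vary little (SD 0.16–0.26 in the first row) against the fixed 0.5 offset.

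**Chance imbalance.** If the arms differ by 10 percentage points in the share on 2.5–3.5, the mean raw value shifts by 0.10 × 0.5 = 0.05 INR units.

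**The case against.** Several points on the other side are sound.

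- **The measure is not empty.** Among patients sharing a midpoint, the raw value orders excursions exactly as distance does, and restricting entry to patients with an out-of-range value already ties each outcome to the individual range. A reader might infer that the two outcomes do not measure depth at all. The documents do not support that: the failure is confined to comparisons across midpoints.
- **There is no systematic bias.** A reader might infer that mixed targets bias the treatment comparison, or that target range should have been a stratification factor. Neither follows. The range is set before randomization, so the arms are balanced in expectation and the tests keep their error rate. A chance imbalance is ordinary sampling variation, at the 0.05-unit scale shown above.
- **Size is uncertain.** A reader might take the larger simulated losses as what this trial will suffer. They rest on an assumed mix and scatter, and for the maximum the effect may be close to nil. Examples built on the 3.0–3.5 target also should not be called typical, since the article presents that range as narrower than usual. The reversals above need only the two common ranges.
- **The remedy is not perfect.** If INR scatter grows with the midpoint, absolute distance still depends somewhat on target level.
- **The wording is soft**, and raw INR has clinical interest of its own. But the article gives depth out of range as the purpose and tests the values formally.

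It might also be said that an analysis plan could settle this. The article does not leave the definition open, however: it fixes the score as the observed value.

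**Conclusion.** The point holds in a limited form. Two tested secondary outcomes are described as showing depth out of range but are scored on a scale that ignores the patient's range. Patients whose midpoints differ can be tied or put in the wrong order. The 0.5-unit offset between the two common ranges follows from the article alone.

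The consequence is a mislabelled quantity plus variance unrelated to treatment. Reading that variance as lost power further assumes that any treatment effect acts on the distance scale. The loss is plausibly modest for the maximum and larger for the minimum, but cannot be fixed without the actual mix of ranges and INR scatter. The primary outcome, TTR, time above and below range, and the sample size are unaffected. This is a worthwhile correction to two secondary definitions, not a threat to the trial's main conclusion.

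**What to change.** Under Secondary outcomes, define the two measures as (maximum INR − the patient's own upper limit) and (the patient's own lower limit − minimum INR), using the midpoint ± 0.5 limits already set under Calculating TTR. Under RCT, compare these distances between arms with the tests already named. Keep raw maximum and minimum INR as descriptive figures.

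The cost is about one sentence in each of the two sections. Each patient's target range and all INR results are already collected, and the limits are already computed for TTR, so no new data are needed and nothing changes for patients or physicians.
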